## Abstract

**Background:**

Implementation strategies are purported to facilitate adoption and use of evidence-based practices (EBPs) across settings. The use of tailored implementation strategies may be particularly effective, as they are selected with the explicit purpose of addressing setting-specific implementation determinants. However, methods to select and tailor implementation strategies, including in community settings, remain understudied. This project will identify and describe implementation strategy mapping methods (ISMMs) from extant peer-reviewed literature and pilot test a method to match implementation strategies with determinants in low-resourced community mental health (CMH) agencies that deliver services to children on the autism spectrum.

**Methods:**

Aim 1: A scoping review, following PRISMA guidelines, will be conducted to identify implementation strategy mapping methods (ISMMs) utilized in child mental health settings. Data extraction will identify and describe each ISMM, including identifying methodological and procedural steps, analyzing the frequency of ISMM use, and identifying outcomes measured in eligible ISMM studies.

Aim 2: Using scoping review findings, select and pilot test one ISMM within five community mental health agencies in Michigan that provide services to autistic children. We will recruit five directors/agency leaders, supervisors, and direct providers at each of the eligible agencies (expected *N* = 25). A sequential explanatory (QUAN➔ QUAL) mixed methods design will be used. Participants will complete a demographics and client survey, as well as a needs assessment to identify implementation determinants. The impact of the ISMM on organizational readiness for change (from pre- to post-ISMM), as well as implementation outcomes of the ISMM (feasibility, acceptability, appropriateness, usability), will be examined. Semi-structured interviews will elicit stakeholder perspectives on the mapping method.

**Discussion:**

The current project aims to advance our knowledge of methods for selecting, tailoring, and mapping implementation strategies to address context-specific determinants to implementation. Additionally, this project will contribute to growing science found at the intersection of implementation science and autism research by utilizing the implementation determinants framework, the CFIR, to guide data collection, analysis, and interpretation of findings. Finally, these findings may support future EBP implementation efforts within low-resourced communities, with the ultimate goal of increasing equity in access to EBPs for autistic children.

Contributions to the literature
This study will explore methods to select and tailor implementation strategies to specifically address implementation barriers and enhance implementation facilitatorsMethods that have been previously used within the context of child mental health service delivery will be identifiedOne method will be tested in the context of community agencies in Michigan that provide services to autistic children from low-income backgroundsFindings will advance our understanding of effective methods to select and tailor implementation strategies so that they are best suited to the settings in which implementation is occurring

## Background

Implementation science seeks to increase the uptake and utilization of evidence-based practices (EBPs) in community-based usual care settings, in an effort to reduce the gap that exists between EBP use in research and practice settings [1]. However, these efforts are not without their challenges, including a lack of systematic and effective implementation processes in community-based usual care settings to facilitate the adoption and implementation of EBPs [2]. Furthermore, while similar challenges may be present across different community-based organizations, each organization faces context-specific implementation barriers and facilitators (i.e., determinants) that are unique to their setting. *Implementation strategies* are defined as a potentially effective way to increase the adoption, utilization, and sustainment of EBPs across settings [3–5]. Furthermore, the use of implementation strategies that are tailored to the organizations in which they will be utilized may be particularly effective in efforts to address implementation determinants and enhance EBP use [6].

A large number of implementation strategies have been identified in extant literature. For example, the Expert Recommendations for Implementing Change (ERIC; [7]) is a commonly used list comprised of 73 distinct implementation strategies. Of importance, it is unknown which of these strategies are most effective within specific service settings or which strategy may address specific organizational barriers (e.g., lack of funding, limited provider training) to EBP implementation, especially within low-resource community service settings [8]. Moreover, although researchers have hypothesized that tailored implementation strategies may be particularly effective for addressing determinants, there is a lack of consensus and guidance in the literature regarding systematic methods for selecting and tailoring implementation strategies for different contexts, including how to map these strategies onto identified implementation barriers and facilitators. Indeed, “enhancing methods for designing and tailoring implementation strategies” has been identified as a high priority aim within the field of implementation science [4].

Implementation researchers have put forward some methods to select and tailor implementation strategies. For example, Powell and colleagues outlined numerous challenges with selecting and tailoring implementation strategies and proposed four methods for matching implementation strategies to determinants: concept mapping, group model building, conjoint analysis, and intervention mapping. These methods have all begun to be utilized within the context of behavioral health service delivery [9]. Other methods include intervention/implementation mapping, which has also been utilized within the healthcare setting [10], as well as the CFIR-ERIC Implementation Strategy Mapping Tool [6] which has been utilized within adult mental health care delivery settings [11]. However, it is currently unknown which specific implementation strategy or set of strategies are likely to be most impactful and feasible in various settings, including in community mental health settings.

In Michigan, community mental health (CMH) agencies are a key service system for providing interventions to autistic children. Moreover, these systems are essential in providing services to autistic children enrolled in the Michigan Medicaid Autism Benefit, who have a household income at or below 133% of the federal poverty level [12]. Although these systems are vital in providing services to autistic children experiencing socioeconomic disadvantage, research indicates that CMH agencies utilize EBPs developed for this population (ASD-EBPs) at a low frequency and with varied intensity [12, 13]. Given the limited use of ASD-EBPs within Michigan CMH agencies, autistic children experiencing socioeconomic disadvantage may receive interventions at a significantly lower rate compared to other children from less disadvantaged backgrounds. Therefore, there is a critical need to investigate methods to systematically and equitably increase the use and delivery of ASD-EBPs within CMH agencies providing services to autistic children from low-resourced communities and experiencing socioeconomic disadvantage [14].

In addition, there is a strong need for the use and delivery of ASD-EBPs for autistic children given the growing prevalence of ASD and potential for associated challenges. ASD is estimated to impact 1.8% of the US population and diagnoses are estimated to be given to 1 in 44 children [15]. ASD is a pervasive neurodevelopmental disorder characterized by social communication differences and the presence of repetitive and/or restricted behaviors [16]. Children on the autism spectrum may be more likely to have difficulty in areas such as social communication, adaptive behavior, and executive functioning compared to neurotypical children, and face considerable systemic barriers to inclusion [17, 18]. Moreover, these difficulties may be exacerbated for autistic children with marginalized identities or experiencing marginalized circumstances (e.g., socioeconomic disadvantage) given the lower rates at which they receive EBPs demonstrated to improve outcomes [13, 19, 20].

Numerous ASD-EBPs have been identified and found to improve both core and co-occurring symptoms (e.g., mental health concerns) for autistic children on average [21]. Naturalistic Developmental Behavioral Interventions (NDBIs) are one category of ASD-EBPs that involve in-session practice that focuses on skill development within a natural environment and during everyday routine activities [21]. Within this ASD-EBP category, Project ImPACT is a parent-mediated NDBI that coaches parents on how to improve their autistic child’s social engagement, social communication, imitation, and play skills within everyday activities [21, 22]. Notable benefits to utilizing NDBIs and parent-training models like Project ImPACT include increased intervention dosage as parents can deliver intervention techniques throughout the day and within varied situations that allows for greater generalization of skills [23]. Further, research evaluating Project ImPACT in both research and community/usual-care settings indicates that this intervention significantly improves communication skills (e.g., greater language acquisition) as well as lowers parental stress [24, 25]. Considering the multiple benefits (e.g., developed in collaboration with autism stakeholders) and demonstrated outcomes of Project ImPACT, it appears a promising fit for use within service systems, like CMH agencies, that have a critical need for feasible and effective EBPs for autistic. However, methods to select and tailor implementation strategies to most effectively implement Project ImpACT within CMH agencies remain unclear.

The current study aims to (a) identify methods that may be used to select and tailor implementation strategies to unique contexts, and (b) evaluate implementation outcomes and organizational impact of one implementation strategy mapping method (ISMM) within the context of CMH agencies. Specifically, this project will focus on implementation efforts within CMH agencies in Michigan that are interested in utilizing Project ImPACT with their autistic clients enrolled in Medicaid benefits. Exploring methods to systematically tailor the implementation process and increase utilization of Project ImPACT within CMH agencies may support increased service equity and ultimately improve patient outcomes for autistic children experiencing socioeconomic disadvantage. The work in the funded project will proceed in two phases with two corresponding specific aims:*Aim 1:* Conduct a scoping review of implementation strategy mapping methods (ISMMs), or methods to select, tailor, and map implementation strategies, to address unique determinants within the context of child mental health service delivery settings.*Aim 2:* Pilot test the use of one ISMM within Michigan CMH agencies providing services to autistic youth whose services are funded by the Medicaid Autism Benefit. Specifically, aim 2 will examine whether the ISMM increases organizational readiness to change from pre- to post-ISMM, and will evaluate implementation outcomes (i.e., perceived feasibility, acceptability, and appropriateness; usability) of the ISMM for selecting and tailoring implementation strategies.

## Method

### Aim 1: conduct a scoping review of implementation strategy mapping methods (ISMMs), or methods to select, tailor, and map implementation strategies to address unique determinants within child mental health service delivery settings

#### Design

The scoping review will facilitate understanding of the extent to which ISMMs have been studied within the context of child mental health service delivery settings, as well as to synthesize the evidence related to ISMMs. Given the large number of discrete implementation strategies, these findings are expected to advance our understanding of how to select strategies that best fit an organization and inform future tailored EBP implementation efforts. Findings will inform which ISMM strategy will be pilot tested during phase 2 (Aim 2).

#### Materials

Covidence software will be utilized to facilitate the title and abstract and full-text review phases of the scoping review. MAXQDA, a qualitative analysis software, will be utilized during data charting.

#### Processes

The scoping review will follow PRISMA guidelines and procedures [26, 27]. The literature search will include three steps to (1) identify common methods, (2) search the literature for identified methods based on the first step, and (3) review references from the included papers to identify additional literature. For details on search terms and databases utilized, see Table 1. Articles identified in the literature review will be screened using a title and abstract review. Finally, articles determined to be eligible following the title and abstract review will be evaluated in the full-text review (Table 2).

**Table 1 Tab1:** Scoping review search terms and databases

Search terms/description	Databases
(“implementation strategy” or “implementation strategies”) AND (“child” OR “pediatric” OR “children”) AND (“mental health service” OR “evidence-based practice” OR “evidence based intervention” or “mental health treatment”)	PsycInfo
	Social Services Abstracts
	PubMed
(“concept mapping” OR “conjoint analysis” OR “group model building” OR “intervention mapping”) AND (“implementation strategy” OR “implementation strategies”) AND (“child” OR “pediatric” OR children) AND (“mental health service” OR “evidence-based practice” OR “evidence based intervention” or “mental health treatment”)	PsycInfo
	Social Services Abstracts
	PubMed
Review references in papers identified via searches 1 and 2 to identify additional relevant literature	N/A

**Table 2 Tab2:** Scoping review eligibility criteria

Inclusion criteria	Exclusion criteria
Title and abstract review	
- Discusses selecting/tailoring/mapping implementation strategies to address implementation determinants - Describes a method for selecting/tailoring/ mapping implementation strategies - Providers work with child populations (< 18) - Implementing mental health practices/interventions	- Article not in English - Providers who work exclusively with adult populations (> 18 years) [If providers work with a range (e.g., 16–25) that includes individuals under 18 years old, *include*] - Non mental-health practices/interventions
Full-text review	
- Includes description of a strategy/method (e.g., concept mapping, intervention mapping) for tailoring implementation strategies to identified determinant - Delivery of MH-EBPs to child populations	- Article not in English Sample details: - Providers who work exclusively with adult populations (18 +) [If providers work with a range (e.g., 16–25) that includes individuals under 18 years old, *include*] - Non mental-health practices/interventions - Article does not provide information on the population of focus ISMM details: - Article does not mention selecting/tailoring/mapping implementation strategies - Article does not describe the method for selecting/tailoring/mapping implementation strategies

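### The Aim 1 searches have no adolescent or youth term although the eligibility criteria admit everyone under 18, so some eligible papers can be missed

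*Protocol article*

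**What the plan says.** The protocol article, Aim 1, Processes, sends the reader to Table 1 for the search ("For details on search terms and databases utilized, see Table 1"), and Table 1 prints complete Boolean strings.

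- **Search 1** joins three blocks with AND: a strategy block ("implementation strategy” or “implementation strategies"), then a population block and an intervention or setting block (together "child” OR “pediatric” OR “children”) AND (“mental health service” OR “evidence-based practice” OR “evidence based intervention” or “mental health treatment").
- **Search 2** has the same three blocks plus a fourth, also joined by AND, that names four mapping methods.
- **Step 3** reviews the reference lists of papers found by the first two searches.

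Table 2 sets eligibility. At title and abstract review the inclusion column has "Providers work with child populations (< 18" and "Implementing mental health practices/interventions". The exclusion column removes providers who see adults only, with a bracketed instruction to include the paper in this case: "If providers work with a range (e.g., 16–25) that includes individuals under 18 years old". The full-text criteria repeat that instruction.

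The Design section of Aim 1 says that the findings will inform which mapping method is piloted in Aim 2.

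**The concern.** A search should be at least as wide as the criteria used to screen what it returns, because screening cannot restore a record that was never retrieved. Here the population block is narrower than the population criterion. A service for 16- to 25-year-olds, the article's own example, may well be described without the words child, children or pediatric. The article itself often calls its target group youth, for example in the Aim 2 heading and in the Discussion, yet the search lacks that word.

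The Aim 1 analysis plan counts how often each method is used, lists common outcomes, and gathers rigor and feasibility data by method. Records lost at the search stage would make those summaries incomplete, and the loss would fall on adolescent and transition-age settings in particular. The section on considerations and limitations expects a possibly sparse literature, so each lost paper matters more. That section names the eligibility criteria as a possible cause of low yield, but not the search terms.

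**Working it through.** The article states no expected yield or recall, so there is no figure to reproduce. The check is a logical one on the printed strings.

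**Inputs** (all from Tables 1 and 2): strategy block S, population block P, intervention block I, method-name block M.

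- Search 1 = S AND P AND I
- Search 2 = M AND S AND P AND I

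**Step 1: can Search 2 recover what Search 1 misses?** Any record that satisfies M, S, P and I also satisfies S, P and I. Search 2 is therefore a subset of Search 1 and adds no records. (In Search 2 the word children is printed without quotation marks; I take it as the same term.)

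**Step 2: test records.** Short constructed sentences, and the article's own abstract, were matched against Search 1 as whole phrases, with hyphen and space treated alike. Assumption A is that plurals are not matched automatically. Assumption B is that a plain added s is matched.

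| Record | Block that decides | A | B |
|---|---|---|---|
| Adolescents only, singular intervention phrase | P fails | missed | missed |
| Youth aged 16–25 only, singular intervention phrase | P fails | missed | missed |
| Children, plural practices and services only | I | missed | found |
| Children, plural interventions only | I | missed | found |
| The article's own abstract | I | missed | found |
| Children, singular phrase (control) | none | found | found |

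The first two rows describe populations that meet the age criterion in Table 2, and they fail under both assumptions. The population gap therefore does not depend on how a platform handles plurals.

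The next three rows do depend on it. The abstract (Background, Methods and Discussion paragraphs) uses the plural of evidence-based practice and none of the four singular phrases. The contributions box printed after it does contain one of the singular phrases and was not part of the test.

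**Step 3: the backstop.** The reference review starts from papers that the first two searches found, and works backwards. It can reach an adolescent-only paper that one of them cites. It cannot reach one that none of them cites, including any paper published later than all of them.

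**Size.** The number of eligible papers worded only in adolescent or youth terms is not in the document and cannot be derived from it.

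**The case against.** Several counter-arguments carry weight.

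- **Scope.** The stated target is child mental health settings, and the 16–25 text is a bracketed qualifier in the exclusion column. It stops screeners from rejecting a mixed-age paper already in hand and does not declare transition-age services a target. This stands in part. The inclusion criterion still covers everyone under 18, though, and that takes in adolescents without any help from the qualifier.
- **Plurals.** A reader might infer that the quoted singulars do lose plural records, because both forms are listed for strategy and for child. The document does not support that. Those two plurals are not formed by simply adding s, whereas service, practice, intervention and treatment all are. The pattern fits authors who expected simple plurals to match at least as well as it fits exact matching. Platform and plural handling are not stated, so this loss is possible, not shown.
- **Extent.** A reader might infer that adolescent papers are systematically missed, have no chance of retrieval, or enter only by chance. That goes too far. Many such papers also use child or children. The search fields and any use of subject headings are not stated, and a journal article may leave those to the full protocol. The reference review is a deliberate step.
- **Consequence for Aim 2.** A reader might infer that the wrong method will be piloted. The Aim 2 Processes section selects on evidence, feasibility and stakeholder engagement, and the limitations section adds expert consultation if no method stands out. The choice does not rest on frequency counts alone, and nothing in the article shows that the best method varies with client age. This stands.

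None of these removes the mismatch between the printed population block and the printed age criterion.

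**Conclusion.** The point holds as a mismatch between two stated rules. As printed, neither database search matches an eligible record whose searched fields contain none of the three population words, and only the reference review can recover it. This rests on reading Table 1 as the full string, as the article invites.

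The plural limb is conditional: it applies only if the platform does not match simple plurals.

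The consequence is a risk of unknown size that the method counts in Aim 1 are incomplete and that the Aim 2 choice is made on a less complete evidence base. It is not evidence that the choice will be wrong. The point is worth acting on because the change is specific and cheap.

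**What to change.** In both searches in Table 1:

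1. Add `adolescen*`, `youth*`, `teen*` and `'young people'` to the population block.
2. Give the four phrases in the third block in plural or truncated form, for example `mental health service*` and `evidence-based practice*`.

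Stating the platform and the fields searched beside the strings would also settle the plural question for the reader.

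The cost is a larger number of records to screen in Covidence. No new software is needed.

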#### Analyses plan

Data extraction will be completed for all articles included following the full-text review. Data will be examined by (a) evaluating the frequency with which each strategy is utilized, (b) conducting content analyses to describe the methods utilized in the literature, and (c) identifying common outcomes measured. Additional data about the rigor of the evidence overall for each method and feasibility data will be gathered.

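### As printed, the second scoping-review search is contained in the first, so the method-specific search step cannot add records

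*Protocol article*

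**What the plan says.** The Aim 1 Processes section sets out a literature search in three steps. The first identifies common methods. The second is described as "2) search the literature for identified methods based on the first step". The third is a check of reference lists.

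Table 1 prints the strings:

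- **Search 1** opens with "implementation strategy” or “implementation strategies”) AND (“child” OR “pediatric” OR “children" and then adds, with AND, the block "mental health service” OR “evidence-based practice” OR “evidence based intervention” or “mental health treatment".
- **Search 2** opens with "concept mapping” OR “conjoint analysis” OR “group model building” OR “intervention mapping”) AND (“implementation strategy” OR “implementation strategies" and then adds, with AND, the same child words and the same mental-health and evidence-based-practice block.
- **Step 3** is "Review references in papers identified via searches 1 and 2 to identify additional relevant literature".

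Both searches use the same three databases. The Background lists the four methods that appear in Search 2. It then goes on: "Other methods include intervention/implementation mapping, which has also been utilized within the healthcare setting", and also names the CFIR-ERIC mapping tool. The Aim 1 analysis plan uses the retrieved papers for, among other things, "evaluating the frequency with which each strategy is utilized". The Aim 1 Design section says the findings inform which mapping method is piloted in Aim 2.

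**The concern.** A search step aimed at particular methods is useful if it can reach papers that a general search cannot. Here that means papers indexed under a method such as concept mapping or intervention mapping whose authors describe their work in other words than implementation strategy. Search 2 keeps the strategy block as a condition, so it looks only inside what Search 1 has already found.

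At stake is the coverage of Aim 1: the inventory of mapping methods, the counts of how often each is used, and the evidence considered when one is chosen for the pilot. The article expects this literature to be sparse (Considerations and limitations), so a few missed papers could matter more than they would in a large field.

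**Working it through.** The plan gives no figure to reproduce. The check is whether any record can satisfy Search 2 without satisfying Search 1.

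**Inputs, all from Table 1**

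| Block | Content | Terms | Search 1 | Search 2 |
|---|---|---|---|---|
| S | implementation strategy / strategies | 2 | yes | yes |
| C | child, pediatric, children | 3 | yes | yes |
| M | mental-health and evidence-based-practice terms | 4 | yes | yes |
| K | four method names | 4 | no | yes |

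Search 1 = S AND C AND M. Search 2 = K AND S AND C AND M.

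**Step 1: containment.** There are 2 + 3 + 4 + 4 = 13 distinct terms, hence 2^13 = 8192 patterns of presence and absence. A block of n terms joined by OR is satisfied by 2^n − 1 of its 2^n patterns.

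- Search 1: 3 × 7 × 15 × 16 = 5040 patterns (K is free, so 2^4 = 16).
- Search 2: 3 × 7 × 15 × 15 = 4725 patterns.
- Matched by Search 2 and not by Search 1: 0. Enumerating all 8192 patterns confirmed this.
- Matched by Search 1 only: 5040 − 4725 = 315, so the containment is strict.

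These are logical patterns, not numbers of papers. They show what is possible and say nothing about yield.

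**Step 2: the one textual difference.** Search 1 prints its child block as "child” OR “pediatric” OR “children", with every word in quotation marks. In Search 2 the word children is unquoted. If a database expanded the unquoted word to one further term, 3 × 15 × 15 = 675 of 2^14 = 16384 patterns would fall outside Search 1. This looks typographical, and nothing in the text presents it as a deliberate broadening.

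**Step 3: what releases the step.**

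- Keep S and add implementation mapping and CFIR-ERIC to K: still 0 patterns outside Search 1.
- Drop S, so that Search 2 = K AND C AND M: 15 × 7 × 15 × 4 = 6300 patterns. Of these, 15 × 7 × 15 × 1 = 1575 have neither strategy term and so lie outside Search 1.

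The strategy block is therefore what makes the step redundant. The length of the method list has no effect while that block is present.

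**The case against.** The strongest reply is that the strategy block matches what the review is looking for. Table 2 requires a paper to discuss selecting, tailoring or mapping implementation strategies, and full-text review excludes papers that do not. Many concept-mapping or conjoint-analysis papers found by a broader Search 2 would be screened out. This stands, and it narrows the loss. It does not remove it, because the criteria concern the concept and not the literal phrase. A paper can meet them in other words, or use the phrase only outside the searched fields.

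A second reply is that a redundant search loses nothing, since Search 1 is the wider net and step 3 follows references. Nothing found by Search 1 is indeed lost. But reference checking starts from papers already found and is only a partial substitute for a search by method name.

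Three stronger readings are tempting, and the documents do not support them:

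- **The omitted method names are a defect in their own right.** They have no retrieval effect while the strategy block stays. Search 1 has no method filter, so it does not shut out papers on implementation mapping. The full name of the CFIR-ERIC tool in the Background itself contains the phrase implementation strategy. The full-text criteria give methods only as examples, so the inventory is not confined to four.
- **The method list was fixed in advance, against step 2.** The four names match the Background list, but the article does not say whether Table 1 shows a preset list or the outcome of step 1.
- **The Aim 2 choice is compromised.** The review only informs that choice. The article also requires feasibility and stakeholder engagement, and provides for expert consultation if no single method stands out. Aim 2 measures and analyses stay the same whichever method is selected.

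**Conclusion.** The point holds as a coverage weakness in Aim 1. As printed, Search 2 is a strict subset of Search 1 and contributes 0 unique records, so step 2 cannot add to what step 1 retrieves. This rests on the two searches using the same fields, limits and dates (the article states no difference) and on the unquoted word not triggering term expansion.

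The containment is certain under those assumptions; the size of the consequence is not. The number of eligible papers missed by both searches cannot be derived from the document. It is bounded by the eligibility criteria and reduced by the reference check. Nothing shows that the frequency counts or the choice of pilot method would change, and no planned Aim 2 analysis is invalidated. The correction is worth making because it is cheap and lets a planned step do its stated job.

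**What to change.** 1. Delete the implementation strategy/strategies block from Search 2, so that it combines method names with the child block and the mental-health and evidence-based-practice block only.
2. With that block gone, add implementation mapping, the CFIR-ERIC tool and any further method found through Search 1 to the method list.
3. Run Search 2 after Search 1, as step 2 describes, and print the child terms identically in both strings.
4. Record which search produced each paper and note it beside the frequency counts. Searching by name can over-represent the named methods. The present design does not have this problem, but the broader search would bring it in.

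The cost is a revised string, a re-run in three databases, and additional titles and abstracts to screen. How many cannot be stated from the document. Eligibility criteria, data extraction and all of Aim 2 are unchanged.
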